**Dietary habits**			
	Have you noticed how different foods affect your glucose levels since using CGM^a^?	Yes No Not sure	
	Have you changed your consumption of sugared beverages since using CGM?	Yes, I have reduced or avoided them No, my consumption is the same I did not consume them before CGM use	
	Have you changed your consumption of high-carbohydrate foods (eg, rice and cereals) since using CGM?	Yes, I have reduced them Yes, I have avoided them No, my consumption is the same I did not consume them before CGM use	
	Do you read nutrition labels more frequently since using CGM?	Yes No I already did this before CGM use	
**Physical activity**			
	Have you increased your physical activity levels since using CGM?	Yes No I was already active before CGM use	
	Are you more likely to engage in physical activity (eg, go for a walk) if you see a rise in your glucose levels?	Yes No Not sure	
**General lifestyle change**			
	Do you feel that using CGM has contributed to a healthier lifestyle overall?	Yes No	
	Since using CGM, how often do you scan to check your glucose levels?	Less than once a day 1-3 times a day 4-6 times a day More than 6 times a day	
	How motivated are you to manage your diabetes since using CGM?	Not motivated Slightly motivated Moderately motivated Highly motivated	
**Medications**			
	Since wearing a CGM, I take my diabetes pills, insulin or both at the right time and as prescribed.	Always Usually Sometimes Rarely Never I already took my medicine at the right time and as prescribed before CGM use	
**Open-ended questions**			
	What specific changes have you made to your diet since using CGM?		—^b^
	What specific changes have you to your physical activity routine since using CGM?		—
	How has CGM affected your overall approach to managing your diabetes?		—

^a^CGM: continuous glucose monitoring.

^b^Not applicable.

#### Safety

Safety endpoints will include an assessment of cutaneous reactions at the site where the CGM sensor is placed. Specific sensor site reactions that will be assessed include erythema, itching, rash, pain, bleeding, bruising, edema, and induration. If any participant experiences a serious cutaneous reaction from the sensor defined as pain, or serious bleeding, they will be withdrawn from the study. If 3 people are withdrawn for that reason, the study will be stopped.

Participants will be screened at the initial visit for any contraindications to using the Abbott Freestyle Libre 2 sensor (including planned magnetic resonance imaging, computed tomography scan, or high-frequency electrical heat (diathermy) treatment during the study time frame.

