### Study Design

This is a 12-week prospective cohort study. Inclusion and exclusion criteria are shown in Textbox 1. Enrolled participants in the intervention group will wear a CGM sensor (Abbott FreeStyle Libre 2; n=20) and receive structured diabetes self-management education and support (DSMES) from a pharmacist in a family medicine clinic. Each participant in the intervention group will have 5 visits with a pharmacist. DSMES will be provided in line with the 2022 National Standards for DSMES [21].

A historical cohort will be used to compare outcomes against the intervention group for the primary outcome. The historical cohort will include participants with T2D and a HbA_1c_ level of ≥8% seen by a pharmacist practicing under a similar scope of practice in a different outpatient clinic within the same health system between January 1, 2020, and January 7, 2024. Participants in this cohort (n=20) will have only used SMBG, and not used CGM within 6 months of the index date (defined as the first visit with a pharmacist during the study time frame). Reporting of research for this cohort study will follow the STROBE (Strengthening the Reporting of Observational studies in Epidemiology) checklist (Multimedia Appendix 1).

Inclusion and exclusion criteria.

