### Study Visits

An overview of activities that will take place at each study visit for participants enrolled in the intervention cohort is shown in Table 1.

**Table 1 table1:** Study activities.

Study activity	Visit 1 (baseline)	Visit 2 (week 2)	Visit 3 (week 4)	Visit 4 (week 6)	Visit 5 (week 12)
Review eligibility	✓				
Obtain informed consent	✓				
Collect patient baseline characteristics	✓				
Collect vital signs (blood pressure, weight, pulse, and oxygen saturation)	✓	✓	✓	✓	✓
Review and collect medications	✓	✓	✓	✓	✓
Assess diet and fitness activity at baseline	✓				
HbA_1c_^a^ blood sample	✓				✓
FSL2^b^ CGM^c^ sensor placement and education	✓				
Provide 5 FSL2 CGM sensors to participants		✓			
Review ambulatory glucose profile and upload into electronic health record		✓	✓	✓	✓
Administer structured diabetes self-management education and support	✓	✓	✓	✓	✓
Provide food and fitness logs	✓				
Assess and collect food and fitness logs		✓	✓	✓	✓
Administer CGM survey		✓	✓	✓	✓
Administer summary of diabetes self-care activities measure	✓				✓
Assess CGM-related adverse events		✓	✓	✓	✓
Provide after-visit summary to participants	✓	✓	✓	✓	✓

^a^HbA_1c_: hemoglobin A_1c_.

^b^FSL2: FreeStyle Libre 2.

^c^CGM: continuous glucose monitoring.

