### Statistical Analyses

Groups will be compared at baseline to determine if any significant differences exist in patient characteristics. The change in the primary and secondary outcomes will be analyzed within and between groups using descriptive statistics (eg, means and SDs for continuous variables such as age, and percentages for categorical variables such as gender). Nonparametric analyses will be used in situations where the variables are not normally distributed. A multivariable regression analysis will be conducted as appropriate to adjust for potential known confounding effects.

The analysis will use an intention-to-treat approach for data analysis. Any participants with missing data or those lost to follow-up will still be included in the analysis. Attempts will be made to match patients on the basis of diabetes medication type and baseline HbA_1c_ in the intervention versus the historical cohorts.

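### The sensor-reaction trigger for withdrawal and stopping is ambiguous about how severe pain must be, and it removes the participant from the study rather than only from the sensor (minor).

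*Protocol article*

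**What the plan says.** The Safety section first lists what will be recorded at the sensor site: "Specific sensor site reactions that will be assessed include erythema, itching, rash, pain, bleeding, bruising, edema, and induration". Pain and bleeding both appear there without a grade.

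It then sets a mandatory rule for the individual: "If any participant experiences a serious cutaneous reaction from the sensor defined as pain, or serious bleeding, they will be withdrawn from the study". A rule for the whole study follows: "If 3 people are withdrawn for that reason, the study will be stopped".

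The exposed group is given under Study Design: "Enrolled participants in the intervention group will wear a CGM sensor (Abbott FreeStyle Libre 2; n=20". The historical cohort used fingerstick monitoring only, so the rule cannot act on it.

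Table 1 under Study Visits schedules "Assess CGM-related adverse events" at visits 2 to 5 (weeks 2, 4, 6 and 12), and an HbA1c sample at baseline and week 12. On handling of the data, Statistical Analyses says: "The analysis will use an intention-to-treat approach for data analysis". It adds that participants with missing data or lost to follow-up remain in the analysis.

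**The concern.** The rule separates serious bleeding from the ordinary bleeding that is merely recorded. It does not clearly do the same for pain. The opening words speak of a serious reaction, but the definition that follows names pain without a grade. A reader can take *serious* as carrying over to pain, or can take the definition at its word. Because the rule is mandatory and can end the study, the difference matters.

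Two things are at stake. Under the literal reading, mild site pain in three people could stop a study with 20 sensor wearers. Under either reading, the participant leaves the study and not only the sensor. The primary outcome is the change in HbA1c to week 12, so a sample not taken after withdrawal is a missing primary outcome, and this rule can cause that in the intervention cohort only.

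**Working it through.** **Wording, side by side**

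| Reaction | In the list of assessed reactions | In the withdrawal trigger |
|---|---|---|
| Bleeding | no grade | serious bleeding |
| Pain | no grade | pain, under the general term *serious cutaneous reaction* |

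If the general term already limited both reactions, the second *serious* before bleeding would be unnecessary. If it did not limit pain, all pain would count as serious, and listing pain as an ordinary reaction would have little purpose. Each reading leaves something unexplained, so the sentence is ambiguous.

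**Inputs**

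- Sensor wearers: n = 20 (Study Design).
- Stopping threshold: 3 withdrawals (Safety), which is 3/20 = 15% of sensor wearers.
- Rate of triggering events per participant, p: not given in the article, so assumed. Pain and serious bleeding count together toward the three, so p can be read as the combined rate.

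The plan states no operating characteristics for the rule, so there is no figure to reproduce.

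**Chance of stopping**

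With independent participants, X is binomial(20, p) and

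P(X ≥ 3) = 1 − (1−p)^20 − 20p(1−p)^19 − 190p²(1−p)^18

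- p = 2%: 1 − 0.6676 − 0.2725 − 0.0528 = 0.0071
- p = 5%: 1 − 0.3585 − 0.3774 − 0.1887 ≈ 0.0755 (from unrounded terms)
- p = 10%: 1 − 0.1216 − 0.2702 − 0.2852 ≈ 0.3231 (from unrounded terms)

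The chance reaches 50% at p of about 13%.

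**Sensitivity to repeated sensors**

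Table 1 lists "sensor placement and education" at visit 1 and "Provide 5 FSL2 CGM sensors to participants" at visit 2. That is 1 + 5 = 6 sensors per person and 20 × 6 = 120 placements. Let q be an assumed pain rate per sensor. If pain is independent across sensors, p = 1 − (1−q)^6. If it always falls on the same people, p = q.

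| q | p, independent | P(stop), independent | P(stop), fully clustered |
|---|---|---|---|
| 0.5% | 3.0% | 2.0% | 0.01% |
| 1% | 5.9% | 10.9% | 0.1% |
| 2% | 11.4% | 40.4% | 0.7% |

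The result turns on two unknowns, the rate and the clustering. The rule is harmless if pain of any grade is rare or confined to the same few people. It matters once pain reaches roughly 1% to 2% per sensor with little clustering.

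**Missing primary outcome**

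Withdrawals under the rule are capped at three, because the third stops the study. Two withdrawals without a stop would put at risk the week-12 value of 2/20 = 10% of the intervention cohort, and three would put 15% at risk. If the study stops, participants not yet at week 12 might also lack the sample. That last step is an assumption, since the article does not say what happens to them.

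**The case against.** The strongest reply is that the sentence does carry a severity qualifier. Its subject is a serious reaction, and ordinary pain sits in the preceding list of reactions that are only assessed. Read together, the two sentences favour serious pain. This stands: it would be wrong to say that pain is wholly unqualified, or that the plan clearly intends to stop for mild pain. What does not fall away is that the definition itself names pain ungraded while grading bleeding.

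Second, the article condenses an IRB-approved protocol that is not shown, and a grading scale for pain may be there. This also stands, so the absence of a scale is not the point. The point is that the definition the article does state can be read in two ways.

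Third, every stopping probability rests on assumed rates. This is correct. A reader might infer from the upper figures that the study is likely to be stopped for trivial pain. The document supports no such statement, because it gives no pain rate.

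Fourth, the harm to the analysis is limited. A reader might infer that withdrawn participants are dropped from the analysis, but Statistical Analyses says the opposite. Practice Setting also places study procedures within routine appointments, where laboratory tests are ordered, so an HbA1c might still arise in care. The article does not say that such a value would be used, so the risk of a missing outcome is reduced but not removed.

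Finally, withdrawing people after a serious device reaction and stopping at three is a legitimate cautious choice. Nothing here argues against the threshold of three.

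**Conclusion.** The point holds as a minor wording defect with one design consequence. The trigger is ambiguous. Serious pain was probably intended, but the literal text lets pain of any grade count toward stopping a 20-person cohort. The size cannot be determined from the document: about 0.7% to 32% under assumed per-participant rates of 2% to 10%, with independence between participants. The ambiguity itself depends on no rate.

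Separately, the rule ends study participation, so it can leave the week-12 HbA1c missing on one side of the primary comparison. Directly, this affects at most three people. It does not amount to excluding them from the analysis, and it changes neither the estimand nor the planned sample size.

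**What to change.** 1. Reword the trigger to severe pain (for example, requiring sensor removal or medical treatment) or serious bleeding, with the pain threshold set by the clinical team. At assumed rates of 1% to 3% for the narrower event, the chance of stopping would be about 0.1% to 2.1%.
2. State that the trigger ends sensor wear, and that follow-up continues with the participant's agreement. The week-12 HbA1c is then still collected and analysed under the stated intention-to-treat approach.

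The second change is separable from the first and worth making even if the pain wording is already settled in the full protocol. The cost is an IRB wording amendment and a slightly less sensitive stopping rule. No visit or sample is added, because the week-12 HbA1c is already in Table 1.

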### Statistical Analyses

Groups will be compared at baseline to determine if any significant differences exist in patient characteristics. The change in the primary and secondary outcomes will be analyzed within and between groups using descriptive statistics (eg, means and SDs for continuous variables such as age, and percentages for categorical variables such as gender). Nonparametric analyses will be used in situations where the variables are not normally distributed. A multivariable regression analysis will be conducted as appropriate to adjust for potential known confounding effects.

The analysis will use an intention-to-treat approach for data analysis. Any participants with missing data or those lost to follow-up will still be included in the analysis. Attempts will be made to match patients on the basis of diabetes medication type and baseline HbA_1c_ in the intervention versus the historical cohorts.

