### Outcomes and Covariates

#### Glycemic Control

To evaluate the primary objective the between-group difference in change in HbA_1c_ levels from baseline to 12 weeks will be compared between the intervention and historical cohort.

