### Strengths and Limitations

Several limitations to this study must be mentioned. First, as an observational study design, the lack of randomization may lead to selection bias. For example, it is possible that participants seeking care and who agree to participate in the intervention group might differ in their overall health status and adherence to medical care versus those who do not seek routine medical care. Furthermore, without randomization, differences in baseline characteristics such as medication adherence, lifestyle factors, and socioeconomic status could impact outcomes. Without randomization, it remains difficult to isolate the true effect of the intervention.

In addition, this study may have low external validity, since pharmacist scope of practice varies widely geographically and among health care systems. Further, concerns such as data from a single site and small sample size must also be considered.

On the other hand, several strengths to this study exist, making it a valuable addition to the literature, such as the measurement of clinically significant outcomes (HbA_1c_) as well as the measurement of CGM-derived metrics, which is lacking in many studies. In addition, our study is also using validated measurement tools (ie, SDSCA) to measure health-behavior change. Finally, although observational, the prospective nature of our study establishes a temporal relationship between exposure (to the intervention) and the outcomes, as well as reflecting real-world clinical practice in a primary care setting.

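### The primary non-randomised HbA1c comparison is described by summary statistics with optional adjustment, although matching on baseline HbA1c is only attempted

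*Protocol article*

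**What the plan says.** The primary outcome is defined under Glycemic Control: "the between-group difference in change in HbA_1c_ levels from baseline to 12 weeks will be compared between the intervention and historical cohort". The comparator is a historical cohort "seen by a pharmacist practicing under a similar scope of practice in a different outpatient clinic within the same health system" (Study Design), with 20 patients in each cohort.

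The Statistical Analyses section contains five relevant statements:

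- On baseline: "Groups will be compared at baseline to determine if any significant differences exist in patient characteristics".
- On the outcomes: "The change in the primary and secondary outcomes will be analyzed within and between groups using descriptive statistics", with means, SDs and percentages as the examples. The Methods paragraph of the Abstract repeats this.
- On distribution: "Nonparametric analyses will be used in situations where the variables are not normally distributed".
- On adjustment: "A multivariable regression analysis will be conducted as appropriate to adjust for potential known confounding effects". No covariates are named.
- On design control: "Attempts will be made to match patients on the basis of diabetes medication type and baseline HbA_1c". No tolerance is given, and no fallback if matching fails.

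Strengths and Limitations concedes that "without randomization, differences in baseline characteristics such as medication adherence, lifestyle factors, and socioeconomic status could impact outcomes".

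**The concern.** The study asks a comparative question of two groups that were not formed by randomisation. The article's stated method for that question is descriptive, and adjustment is discretionary. An analyst who reported only the unadjusted difference in mean change would be following the plan. So would one who looked at both results and then decided that adjustment was appropriate.

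Change in HbA1c usually depends on where a patient starts: higher values tend to fall further. Both cohorts are selected at HbA1c of 8% or more, so regression towards the mean is expected in each, and its amount depends on the baseline level. If the cohorts differ at baseline after matching, the unadjusted change difference carries part of that difference as apparent effect. The plan treats baseline HbA1c as a confounder, since it proposes to match on it, but it does not commit to adjusting for it.

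At stake are the validity of the primary estimate, its precision in a study of 40, and freedom from a choice of analysis made after the data are seen.

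**Working it through.** The plan gives no effect size, SD, alpha or power value, so it has no figure to reproduce. From the article I take only 20 per cohort. Everything else below is an assumption: two-sided 5% test, baseline SD 1.0 to 2.0 points (central value 1.5), slope of 12-week on baseline HbA1c 0.3 to 0.7 (central value 0.5), baseline-to-follow-up correlation r of 0.3 to 0.6, approximate normality, and no dropout.

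**1. What a baseline test can show.** Power of a two-sample t-test, 20 versus 20 (noncentral t, 38 degrees of freedom):

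| True imbalance | Power |
|---|---|
| 0.3 SD | 15.2% |
| 0.5 SD | 33.8% |
| 0.8 SD | 69.3% |

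The normal approximation gives 16%, 35% and 72%. An imbalance of half an SD would be missed about two times in three.

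**2. Bias in the unadjusted change difference.** If baseline HbA1c were the only confounder and its relation to follow-up linear, the size of the bias is

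imbalance (in SD) × baseline SD × (1 − slope).

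- 0.1 SD left after matching: 0.1 × 1.5 × 0.5 = 0.075, about 0.08 points.
- 0.5 SD: 0.5 × 1.5 × 0.5 = 0.375, about 0.38 points.
- 0.5 SD, smallest value in the assumed range: 0.5 × 1.0 × (1 − 0.7) = 0.15 points.
- 0.5 SD, largest value: 0.5 × 2.0 × (1 − 0.3) = 0.70 points.

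If the intervention cohort starts higher, the bias favours the intervention; if it starts lower, the bias goes against it.

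**3. Simulation check.** 6,000 runs per scenario, no true effect, baseline SD 1.5, slope 0.5, residual SD 1.2, intervention cohort higher at baseline:

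| Imbalance (points) | Unadjusted bias | Unadjusted false positives | Baseline-adjusted bias | Baseline-adjusted false positives |
|---|---|---|---|---|
| 0.50 | −0.25 | 8.7% | 0.00 | 5.2% |
| 0.75 | −0.37 | 13.3% | 0.00 | 5.2% |
| 1.00 | −0.49 | 19.2% | 0.00 | 5.4% |

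Adjusting only when the baseline test is significant leaves a bias of −0.14 to −0.16 in these scenarios. The plan does not state that rule; the result shows what would follow if it were used.

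**4. Precision.** With equal SDs at the two visits and balanced baselines, the variance of the adjusted difference divided by that of the change difference is

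(1 − r²) / [2(1 − r)] = (1 + r)/2.

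This is 0.65 at r = 0.3 and 0.80 at r = 0.6, a saving of 35% to 20%. An imbalance of 0.5 SD inflates the adjusted variance by about 1 + 0.5²/4 = 1.06. The ratios become 0.65 × 1.06 = 0.69 and 0.80 × 1.06 = 0.85, a saving of 31% to 15%. Across both cases the gain is roughly 15% to 35%.

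For scale, the 95% half-width for an unadjusted change difference is t(0.975, 38) × SD × √(2/20). That is 0.64, 0.96 or 1.28 points for an SD of change of 1.0, 1.5 or 2.0.

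**The case against.** **Matching.** The strongest reply is that the plan already tries to balance the variable at issue. If matching works, a 0.5 SD imbalance is not the relevant case, and at 0.1 SD the bias is only about 0.08 points. This stands and limits the size of the concern. It does not remove it, because matching is only attempted and nothing is stated for when it fails.

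**No stated gate.** A reader might infer that the baseline tests decide whether regression is run, or that a normality check sends the primary outcome to a rank test without covariates. The text does not say so. These are separate sentences and none is linked to another by a rule. What can be said is narrower: adjustment is discretionary, and nothing rules out using those checks to exercise the discretion.

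**Condensed article.** The covariate list, the exact model and the interval method may stand in an analysis plan that is not shown, so their absence is no fault. The point rests on what the article does state: a descriptive outcome analysis and optional adjustment.

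**Change scores against baseline adjustment.** In non-randomised groups the two estimators rest on different untestable assumptions. This is true in general but carries little weight here, since both cohorts are selected on a high HbA1c and the plan itself treats baseline HbA1c as a confounder.

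**Disclosure and purpose.** The article admits the lack of randomisation, the risk of baseline differences and the small sample, and says under Future Directions that the data are to support a larger randomised trial. That argues for a lower rating, not for leaving the wording as it is.

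**Conclusion.** The concern holds in a limited form. The stated plan permits an unadjusted primary result for a non-randomised contrast and leaves the decision to adjust open until the data are seen. The resulting bias is about 0.08 points if matching leaves 0.1 SD and 0.38 points if it leaves 0.5 SD, at an assumed baseline SD of 1.5 and slope of 0.5. At 0.5 SD it runs from 0.15 to 0.70 points over the assumed ranges. Baseline adjustment would also save roughly 15% to 35% of the variance for r of 0.3 to 0.6. None of these inputs is in the article.

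A reader might infer that a bias near 0.4 points is expected and would by itself reproduce the low end of the 0.4 to 1.8 point reductions cited under Comparison to Previous Work. The article supports neither step. The 0.38 figure needs a sizeable imbalance to survive matching. The cited range is a reduction associated with pharmacist-led CGM and is not stated to be a contrast with pharmacist care without CGM.

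This should be fixed. It is an almost free improvement to the primary analysis rather than a flaw that makes the study unsound.

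**What to change.** State one primary analysis that is fitted whatever the data look like: a linear regression of 12-week HbA1c on cohort, continuous baseline HbA1c, and diabetes medication type in a coarse coding fixed in advance. If matching is achieved, allow for the pairs, for example with standard errors clustered on pair; separate pair indicators would use 20 − 1 = 19 degrees of freedom. Report the adjusted difference with a 95% confidence interval.

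Keep the unadjusted change difference and any rank test as sensitivity analyses. Say that neither baseline significance tests nor normality checks will be used to choose the primary analysis.

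The cost is wording and a few degrees of freedom. The two-group comparison has 38; baseline HbA1c takes one, and a medication factor takes one fewer than its number of levels (with three levels, for example, 38 − 1 − 2 = 35 remain). No new data are needed: the primary outcome already requires both HbA1c values, and the matching already requires medication type.

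The model will not deal with clinic, calendar time, adherence, lifestyle or socioeconomic status. Strengths and Limitations already names the last three among baseline differences; it should add clinic and calendar time, and say that confounding by all of these remains after adjustment.
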